**Fig 1 pone.0357577.g001:**
[figure not shown]
Study design and comparison groups. Schematic overview of the retrospective multicentric cohort study evaluating the impact of GLP-1 RA therapy on patients with IPMNs. Four study groups will be included according to IPMN diagnosis and GLP-1 RA exposure: patients with IPMN treated with GLP-1 RAs, patients with IPMN not treated with GLP-1 RAs, patients without IPMN treated with GLP-1 RAs, and patients without IPMN and without GLP-1 RA exposure (general population). The primary outcome (1) is the progression of radiological IPMN characteristics according to the Kyoto 2023 Consensus criteria. Secondary outcomes include longitudinal changes in serum CA19−9 and CEA levels (2) and the incidence of acute pancreatitis (3). We hypothesize that GLP-1 RA therapy is not associated with an increased progression of IPMN radiological features or adverse pancreatic outcomes compared with patients not exposed to GLP-1 RAs.

A list of patients diagnosed with IPMNs will be compiled (List A), and this group will then be cross-referenced with data from patients who have been treated with GLP-1 RAs (List B). ICD-10 codes, keywords like IPMN and ATC medication codes will be used to identify the patients and compile the two lists (S1 File). This method will allow us to identify the subset of patients in whom both IPMN and GLP-1 RA treatment are present. The same number of patients will be randomly extracted from the two lists. For example, if 3 patients with GLP1-RA and IPMN are extracted in the HFR dataset, then 3 patients will be extracted in List A and 3 in List B. The same procedure will be carried out for the other two institutions. For the no GLP-1 RA & no IPMN group, the proportion of AP will be generalized to the incidence in the general population.

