### Sample size and statistical analysis

#### Sampling plan.

The sample size is expected to be between 10 and 20 patients for the condition with GLP-1 RAs and IPMN, due to the rare nature of the patient population with both IPMN and GLP-1 RA use. The other conditions (GLP-1 RA & no-IPMN, no GLP-1 RA & IPMN) will match in sample size the above-mentioned condition as it is the most stringent. This design ensures to isolate the interaction effect of GLP-1 RA and IPMN while ensuring proper statistical power. Indeed, a-priori power analysis computed with G*Power [22] shows that for our smallest estimation of effect size (i.e., 10–30 patients per condition, 30–60 in total), a 2x2 ANOVA detects a significant medium effect size with a power if 80% and an alpha of 0.05.

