#### Analysis plan.

H1) We expect significantly more occurrences of change in at least one of the criteria from the Kyoto 2023 Consensus (see Outcomes section) [1] from patients with GLP-1 RA & IPMN than patients with no GLP-1 RA & IPMN, as assessed by a one-sided test of two proportions. H2) We expect significantly greater changes in the CEA (H2a) and CA19−9 (H2b) serum tumor markers over time induced by GLP-1 RA, as assessed by the interaction term of the within-factor Time and the between-factor Group (GLP-1 RA & IPMN vs. no GLP-1 RA & IPMN). H3) We expect significantly different incidence of AP driven by GLP-1 RA and IPMN, as assessed by a Chi-square test across all conditions (GLP-1 RA & IPMN, no GLP-1 RA & IPMN, GLP-1 RA & no IPMN).

Timing of progression: T0 will be defined as the first available follow-up examination for patients with IPMN who were not treated with GLP-1 RAs, and as the first available follow-up examination after initiation of GLP-1 RA therapy for patients with IPMN who received GLP-1 RAs.

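### Cutting both comparator groups at random to the 10–20 of the co-exposed group does not secure power; for acute pancreatitis (H3) it only discards comparator information, and the 80% figure does not reproduce

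*Protocol article*

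**What the plan says.** The Study design section of the protocol article (text after the Fig 1 legend) builds two lists. "A list of patients diagnosed with IPMNs will be compiled (List A"), and List B holds patients treated with GLP-1 RAs. Both come from a search: "ICD-10 codes, keywords like IPMN and ATC medication codes will be used to identify the patients and compile the two lists". Patients on both lists form the co-exposed group. The lists are then sampled: "The same number of patients will be randomly extracted from the two lists", site by site, in the number of co-exposed patients found at that site.

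The Sampling plan gives the size: "The sample size is expected to be between 10 and 20 patients for the condition with GLP-1 RAs and IPMN". The other two sampled groups "will match in sample size the above-mentioned condition as it is the most stringent". It presents this as securing adequate power and supports it with a G*Power result for "10–30 patients per condition, 30–60 in total", namely that "a 2x2 ANOVA detects a significant medium effect size with a power if 80% and an alpha of 0.05".

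The Analysis plan applies the same three groups to H3: "We expect significantly different incidence of AP driven by GLP-1 RA and IPMN, as assessed by a Chi-square test across all conditions". The fourth group (neither IPMN nor GLP-1 RA) is not sampled; a general-population incidence stands in for it. Nothing in the article keeps the undrawn list patients for H3.

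**The concern.** Only the co-exposed group is described as rare. Its rarity is then used as the reason to shrink the other two groups to the same size. Equal allocation is efficient when the total is fixed and can be divided freely. Here one group is fixed by nature, and reducing the others cannot raise power.

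For H1 and H2 the cut has a practical defence, since each added patient means scans to be re-read by two radiologists or marker series to be assembled. For H3 that defence is weaker, because acute pancreatitis (AP) can be taken from existing records.

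AP is a listed secondary outcome and one of the safety questions in the Introduction. With 10–20 patients per comparator the reference risk is poorly measured, and a table with few or no comparator events could be read as reassurance when it carries little information either way.

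**Working it through.** **1. The stated 80%.** Inputs: 2x2 ANOVA, medium effect, alpha 0.05, 30–60 patients in total (Sampling plan). "Medium" is taken as f = 0.25, the usual G*Power convention (assumption). Power = P(F′ > F crit), with 1 and N − 4 df and noncentrality N·f².

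- N = 30: noncentrality 30 × 0.0625 = 1.875, power 26%.
- N = 60: noncentrality 3.75, power 48%.
- 80% needs N = 128.

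A repeated-measures group-by-time interaction with correlation 0.5 reaches 80% at N = 34. That might describe H2, but it is not the named test and says nothing about H3. A chi-square with 2 df and w = 0.3 gives 29% at N = 30 and 54% at N = 60. The inputs also disagree: 10–20 per condition in one sentence and 10–30 in the next, and 3 × 30 = 90, not 60.

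**2. Chance that a comparator shows no AP case.** P(0) = (1 − p)^n. The article gives no AP risk, so p is assumed.

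| Comparator AP risk | n = 10 | n = 20 |
|---|---|---|
| 1% | 90% | 82% |
| 2% | 82% | 67% |
| 3% | 74% | 54% |
| 5% | 60% | 36% |
| 10% | 35% | 12% |

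P(0) exceeds one half when p < 1 − 0.5^(1/n), which is 6.7% for n = 10 and 3.4% for n = 20.

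**3. What an empty comparator leaves open.** The exact two-sided 95% upper limit for 0/n is 1 − 0.025^(1/n): 31% (n = 10), 22% (n = 15), 17% (n = 20), 3.6% (n = 100). The next point needs no assumed risk. If a comparator of equal size has no case, two-sided Fisher significance needs 5 co-exposed cases at n = 10, 15 or 20 (p = 0.033, 0.042, 0.047). Against an illustrative 2/100, 2 cases suffice at n = 10 (p = 0.041) and 3 at n = 15 or 20 (p = 0.016, 0.032).

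**4. Pairwise power.** Two-sided Fisher test by full enumeration, 15 co-exposed patients against one comparator group. List sizes are not in the article, so the larger numbers are assumptions.

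| Co-exposed vs comparator risk | 15 | 30 | 100 | 300 |
|---|---|---|---|---|
| 20% vs 3% | 11% | 40% | 60% | 62% |
| 15% vs 2% | 5% | 28% | 50% | 52% |
| 10% vs 2% | 1% | 12% | 29% | 30% |
| 15% vs 5% | 3% | 16% | 27% | 30% |

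**5. The planned test.** Three-group Pearson chi-square, 200,000 simulated data sets, 10% vs 2% in both comparators. At equal sizes, power is 5% (n = 10) and 17% (n = 20). With 100–500 per comparator it is 33–35% (10 co-exposed) and 45–52% (20 co-exposed). Part of this gain is size inflation: with no true difference and 1% risk, 10 co-exposed patients and 500 per comparator, the asymptotic test rejects in 9.5% of data sets. It can also mislead at the planned sizes: 3/10, 0/10, 0/10 gives p = 0.036 over three groups, while Fisher for 3/10 against 0/10 gives p = 0.21.

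**The case against.** The strongest reply is that the co-exposed group, not the cut, limits H3. This stands. Even with 300 comparators, a five-fold excess (10% vs 2%) reaches only about 30% pairwise power, and the gain flattens beyond about 100.

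The article also admits limited power, in the abstract and the Discussion, and calls the results hypothesis-generating. That also stands, and AP is a secondary outcome. But neither passage names the random cut as a cause, and the Sampling plan says the opposite.

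Using more comparators is not free. The lists are still to be compiled and their sizes are unknown. A code or keyword hit is not eligibility, which also needs consent and available laboratory and imaging records (Population). The Discussion warns that GLP-1 RA prescriptions may be missing from hospital records, so non-exposure has to be checked. The Radiological evaluation section also uses imaging to look for signs of pancreatitis. The Positive controls section requires balance in age, BMI and number of follow-ups, which a whole-list comparison would not give by itself. All of this bears on how the remedy is built; none of it supports the cut as a way to gain power, since a random draw equalises numbers and not characteristics.

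A reader might infer that the comparators will mostly show no AP case. The article does not support that as a fact: it states no risk, and at 5% with n = 20 the probability is 36%. Nor are the pairwise Fisher figures the power of H3 as planned; for 20% vs 2% the planned chi-square gives 25% (n = 10) to 53% (n = 20) even under the cut.

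**Conclusion.** The concern holds in a limited form. The rationale for cutting both comparator groups to the size of the co-exposed group is wrong. The 80% does not reproduce for the named ANOVA at f = 0.25 (26–48% at N = 30–60), and that calculation does not cover H3.

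For H3 the cut is an avoidable loss: pairwise power for 20% vs 3% goes from 11% to 40% with as few as 30 comparators. For 10% vs 2% the planned chi-square goes from 5–17% to about 33–52%, partly through size inflation. These sizes rest on assumed AP risks and assumed list sizes.

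The documents do not support the stronger reading that the cut alone empties H3 or that removing it would make H3 well powered. What is gained is a measured comparator risk and a less uninformative contrast, and H3 remains exploratory.

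**What to change.** - Keep the equal-size draw for H1 and H2.
- For H3, use all eligible, consented List A patients without GLP-1 RA and List B patients without IPMN, or a stated number per co-exposed patient if checking capacity is limited. Most of the gain is reached well before several hundred.
- Ascertain AP by one rule in every group (coded episode confirmed on the chart). Report imaging signs of pancreatitis separately, as a description.
- Define the start and end of observation in each group, account for differing observation time, and adjust or stratify for age and BMI as far as the event count allows.
- Report exact confidence intervals for each group, or an exact test, in place of the asymptotic chi-square.
- Delete the statement that matching the smallest group ensures power. Restate the 80% with its design, effect size and total, and reconcile 10–20 with 10–30 per condition.

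Cost: eligibility and exposure checks on more records, and chart confirmation of coded AP episodes. AP then rests on coding plus chart review. No new enrolment and no extra scan reads are needed.

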## Methods

### Study design

This is a retrospective multicentric cohort study conducted at three Swiss Hospitals, Cantonal Hospital of Fribourg (HFR), University Hospital of Geneva (HUG) and University Hospital of Bern (Inselspital), to evaluate the effects of GLP-1 RA therapy on patients with IPMNs. Data from January 2010 to July 2026 will be reviewed.

The primary focus of the study will be to investigate the impact of GLP-1 RA therapy on the progression of IPMNs, specifically examining changes in IPMN radiological characteristics such as described in the Kyoto 2023 Consensus [1]. Additionally, the study will assess the variations in serum tumor markers such as CA19−9 and CEA and incidence of acute pancreatitis in patients undergoing GLP-1 RA treatment. The progression of IPMNs to high-grade dysplasia or invasive carcinoma, the need for surgical intervention or changes in IPMN surveillance protocols will also be assessed.

Data already collected from medical records, laboratory results, and imaging studies will be reviewed for patients diagnosed with IPMNs and treated with GLP-1 RAs for diabetes or obesity between 01.01.2010 and 31.07.2025 at HFR, HUG, and Inselspital. To assess the impact of GLP-1 RA exposure in patients with IPMNs, we will also include control groups without GLP-1 RA exposure and without IPMNs, resulting in four groups defined by a 2 × 2 factorial design (GLP-1 RA exposure: yes/no × IPMN: yes/no) (Fig 1).

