## Discussion

This study aims to provide preliminary insights into the potential impact of GLP-1 RAs therapy on the progression and clinical outcomes of IPMNs. A better understanding of the relationship between GLP-1 RA exposure and IPMNs may help address current safety uncertainties and support clinical decision-making in this complex patient population.

Several limitations must be acknowledged. The retrospective design introduces inherent risks of selection and information bias, while the relatively small sample size limits statistical power and the ability to detect modest associations. Patient identification may be incomplete, as GLP-1 RAs prescriptions may have been initiated by healthcare providers outside the participating institutions or inconsistently documented and therefore not fully captured in institutional records. Furthermore, initiation of the treatment may have been influenced by clinical judgement and recent literature implying a possible link between GLP1 Ras use and pancreatitis or pancreatic cancer, introducing potential prescription bias. In addition, the relatively recent and rapidly increasing widespread use of GLP-1 receptor agonists may limit the ability to assess long-term effects on IPMN evolution. As a result, potential late modifications or clinically relevant changes may not yet be detectable within the available follow-up period.

Therefore, the results should be interpreted as hypothesis-generating. Despite these limitations, this study addresses an important gap in the current literature and may serve as a basis for future prospective, multicentre studies.

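### Acute pancreatitis is compared as a proportion of patients with no time at risk, and the unsampled fourth group takes a population incidence with no period or scaling

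*Protocol article*

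**What the plan says.** AP is one of the two outcomes listed under Secondary outcomes, where it is named as an incidence with no window or denominator.

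- **Test (Analysis plan, H3):** "We expect significantly different incidence of AP driven by GLP-1 RA and IPMN, as assessed by a Chi-square test across all conditions". The bracket that follows lists three groups: "GLP-1 RA & IPMN, no GLP-1 RA & IPMN, GLP-1 RA & no IPMN".
- **Fourth group (Study design, paragraph after Fig 1):** the group with neither IPMN nor GLP-1 RA is not sampled. Instead, "the proportion of AP will be generalized to the incidence in the general population".
- **Record window (Study design):** "Data from January 2010 to July 2026 will be reviewed". The same section also gives 31.07.2025 as an end date. Either way the window is about 15.6 to 16.6 years.
- **Balancing (Positive controls):** age, BMI and the number of follow-ups are to be balanced, the last by ignoring surplus visits. Elapsed time is not mentioned.
- **Time origin (Analysis plan, Timing of progression):** in unexposed IPMN patients, T0 is the earliest follow-up on record. Exposed IPMN patients have a different anchor: "as the first available follow-up examination after initiation of GLP-1 RA therapy for patients with IPMN who received GLP-1 RAs". No origin is given for GLP-1 RA users without IPMN, although they enter H3.

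**The concern.** AP can be recorded only while a patient is under observation. A chi-square on patients treats someone observed for one year and someone observed for ten as equal opportunities for an event. If the groups differ in years observed, part of any difference in AP proportion measures length of record.

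The fourth group raises the same problem in another form. A proportion accumulated over several years and a population incidence are on one scale only if the period is stated and matched. The protocol treats them as interchangeable and gives no period.

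Both matter because the Introduction presents AP as one of the unresolved safety questions behind the study. An AP contrast that reflects observation time could suggest harm or protection when neither exists.

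**Working it through.** **Figure to reproduce.** There is none for AP. The only power figure (80%, Sample size and statistical analysis) is for a 2x2 ANOVA and does not bear on H3.

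**Inputs from the protocol.** 10 to 20 patients in the GLP-1 RA and IPMN group, with the two other sampled groups matched to it; a chi-square across three groups; the record window above.

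**Assumptions.** The protocol gives no AP rate and no years of observation. I take a constant rate h of 0.005 to 0.05 per person-year (0.0005 at the lowest) and 2 to 8 years of observation. For the population rate I take 20 to 100 per 100,000 per year.

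**Step 1: one true rate, unequal years.** The expected proportion with AP over T years is 1 − exp(−hT).
- At h = 0.02, 2 years gives 1 − exp(−0.04) = 3.9% and 8 years gives 1 − exp(−0.16) = 14.8%, a ratio of 3.8.
- For h from 0.0005 to 0.05, the ratio is 3.5 to 4.0 for 8 against 2 years, and 2.3 to 2.5 for 5 against 2 years.
- Events per person-year have an expected ratio of 1.0 in every one of these cases.

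**Step 2: the sign depends on the window, which is not fixed.** Take h = 0.02.

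| AP counted | Exposed | Unexposed | Ratio |
|---|---|---|---|
| After drug start only, 2 vs 8 years, no drug effect | 3.9% | 14.8% | 0.27 |
| After drug start only, 2 vs 8 years, true doubling: 1 − exp(−0.08) | 7.7% | 14.8% | 0.52 |
| Whole record, 8 years (last 2 on drug) vs 8 years, true doubling on drug: 1 − exp(−0.02×6 − 0.04×2) | 18.1% | 14.8% | 1.23 |
| Whole record, 8 years (last 2 on drug) vs 2 years, no drug effect | 14.8% | 3.9% | 3.8 |

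Counting only after drug start can make a harmful drug look protective. Counting the whole record attributes pre-exposure AP to the drug: this dilutes a true effect in the third row and creates a false one in the fourth.

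**Step 3: effect on the test.** The three-group chi-square was simulated at nominal 0.05 with one common rate, 20 per group and 100,000 runs.

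| Rate per person-year | Rejection, 2/2/2 years | Rejection, 2/8/2 years | Events expected in total, 2/8/2 |
|---|---|---|---|
| 0.005 | 0.002 | 0.03 | 1.2 |
| 0.01 | 0.009 | 0.10 | 2.3 |
| 0.02 | 0.027 | 0.21 | 4.5 |
| 0.05 | 0.039 | 0.50 | 10.4 |

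False rejection exceeds 5% only at the higher rates. At 0.005 there are too few events to reject, but the expected proportions still differ about fourfold.

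**Step 4: population figure.** If it is an annual rate h used unscaled, the ratio with no true difference is (1 − exp(−hT))/h. For h = 0.0002 to 0.001 this is 2.0 at T = 2, 5.0 at T = 5 and 8.0 at T = 8. In counts it is small: 20 patients × 8 years × 0.001 = 0.16 expected cases.

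**The case against.** Several stronger readings are tempting, and the protocol does not support them.

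- **That GLP-1 RA users are observed for less time, so H3 hides a true increase.** A reader might infer this from the two T0 rules and from the Discussion's remark that "the relatively recent and rapidly increasing widespread use of GLP-1 receptor agonists may limit the ability to assess long-term effects". But the T0 rules are headed Timing of progression, cover only the two IPMN groups and are not tied to AP. The Discussion sentence goes on to concern IPMN evolution, not AP observation. The Introduction dates GLP-1 RA use in diabetes from 2005, before the window opens, so some exposed patients could contribute many years.
- **That the H3 error and the population error run in opposite directions.** This depends on the first inference and fails with it.
- **That the population figure enters the H3 test.** The bracket lists only the three sampled groups, and no test against the population is stated.
- **That the 2- to 8-fold excess will occur.** The protocol gives no unit, and incidence can mean cumulative incidence. The multiples hold only for an unscaled annual rate.

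Other points also carry weight. Trimming visits may narrow a gap in years. Events will be few: at 20 per group and h = 0.02, 2 years gives 20 × 0.039 = 0.8 expected cases and 8 years gives 20 × 0.148 = 3.0. Sparse data alone prevent firm conclusions about AP, and the Discussion already calls the results hypothesis-generating. Details of risk windows are often left to an analysis plan.

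These points limit the size and direction of the claim but do not remove it. The test and the comparator are both fixed in the protocol, and neither has a time denominator. An analysis plan that followed this wording would carry the problem forward.

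**Conclusion.** The concern holds in limited form. As written, the AP comparison in H3 ignores time at risk, and the fourth group's AP figure equates a per-patient proportion with a population incidence of unstated period. Balancing visits does not equalise years, because visit intervals can differ and nothing says that AP counting stops at the last retained visit.

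If mean years differ, the proportions are distorted roughly in the ratio of those years at low rates. If they are equal, the sampled groups are not distorted in this way, but the population comparison still needs a matched period. The size rests on assumed constant rates and assumed durations, and the sign is undetermined until an AP window is fixed. This should be changed before analysis, but it affects a secondary outcome and not the primary one.

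**What to change.** **Analysis plan, H3.** Define the AP measure as first episodes divided by person-years in the patient's group state. For exposed patients, time starts no earlier than GLP-1 RA initiation. It ends at AP, death, last record or data cut-off. State the origin for all three sampled groups. Replace the chi-square by an exact comparison of rates: given the total number of episodes, their split across groups is tested against probabilities proportional to person-years.

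**Study design, paragraph after Fig 1.** Replace the sentence on the fourth group. Name a source of age- and sex-specific population AP rates, apply them to the person-years of each sampled group to obtain expected cases, and report observed/expected with an exact Poisson interval.

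**Cost.** No extra patients or procedures. First and last observation dates and drug start dates must be extracted. Some start dates will be uncertain, since the Discussion concedes that prescriptions made outside the three hospitals may be missed. Rates do not cure small numbers: with no event among 20 patients followed for an assumed 2 years (40 person-years), the exact two-sided 95% upper limit is −ln(0.025)/40 = 3.69/40 = 0.092 per person-year. The AP result should be labelled descriptive.
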